**Figure 1 F1:**
[figure not shown]
Flow diagram of the study design.

Eligible patients will be stratified into two parallel cohorts based on voluntary consent to participate in the remote monitoring intervention. Patients in the intervention group will wear the EmbracePlus (Empatica Inc.) mini-invasive device continuously for six months (20, 21). This CE-certified wearable device captures a comprehensive set of physiological parameters, including SpO₂, HRV, EDA, respiratory rate, peripheral skin temperature, and sleep quality, which are transmitted in real time to the SMART-CARE digital platform (20–22). The collected data will be processed through AI algorithms capable of identifying abnormal trends and generating alerts to prompt timely clinical action (32–34); moreover, these data will serve a broader purpose within the SMART-CARE project: to support the development of a novel diagnostic and prognostic algorithm. By integrating biometric signals with clinical, instrumental, and biochemical information, the SMART-CARE platform will apply advanced machine learning techniques to generate predictive models aimed at identifying the clinical trajectory of CHF patients and optimizing personalized care strategies.

Patients in the control group will undergo standard chronic heart failure (CHF) follow-up as per clinical guidelines, including in-person visits every three months, electrocardiography (ECG), echocardiography, and laboratory evaluation [e.g., B-type Natriuretic Peptide (BNP), N-terminal pro-B-type Natriuretic Peptide (NT-proBNP), renal and hepatic function, serum electrolytes]. All patients, regardless of group assignment, will be evaluated at baseline, 3 months, and 6 months.

Patients with NYHA class IV symptoms, anticipated heart transplantation or ventricular assist device implantation within 6 months, severe renal impairment (estimated Glomerular Filtration Rate - eGFR <30 mL/min/1.73 m^2^), terminal illness, or inability to comply with study procedures will be excluded (Table 1).

**Table 1 T1:** Inclusion and exclusion criteria for the SMART-CARE study.

Inclusion criteria	Exclusion criteria
Age ≥ 18 years (male or female)	NYHA class IV symptoms
Confirmed diagnosis of CHF ≥ 6 months prior to screening	Planned heart transplant or VAD implantation within 6 months
NYHA functional class I, II, or III	Severe renal impairment (eGFR < 30 mL/min/1.73 m^2^) or dialysis dependency

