### Outcomes

2.4

Both groups will undergo assessments at baseline, 3 months, and 6 months, including evaluations of functional status, echocardiographic parameters, biochemical markers (e.g., BNP, NT-proBNP, renal function), and quality of life assessed using the Kansas City Cardiomyopathy Questionnaire (KCCQ) (36–39) (Table 2).

**Table 2 T2:** SMART-CARE outcome measures by timepoint.

Outcome type	Outcome measure	Domain	Baseline	3 months	6 months
Primary	Change in Hospital Admissions	Clinical Events			✔
Secondary	Change in Quality of Life (KCCQ Score)	Quality of Life	✔	✔	✔
Secondary	Adverse Effects of CHF Therapy	Safety			✔
Secondary	Change in BNP Levels	Biochemical	✔	✔	✔
Secondary	Change in NT-proBNP Levels	Biochemical	✔	✔	✔
Secondary	Change in Serum Creatinine	Biochemical	✔	✔	✔
Secondary	Change in eGFR	Biochemical	✔	✔	✔
Secondary	Change in Serum Sodium	Biochemical	✔	✔	✔
Secondary	Change in Serum Potassium	Biochemical	✔	✔	✔
Secondary	Change in Serum Chloride	Biochemical	✔	✔	✔
Secondary	Change in HRV	Functional (ECG)	✔	✔	✔
Secondary	Change in Respiratory Rate	Functional (ECG)	✔	✔	✔
Secondary	Change in LVEF	Echocardiographic	✔	✔	✔
Secondary	Change in E/A Ratio	Echocardiographic	✔	✔	✔
Secondary	Change in LV End-Diastolic Volume	Echocardiographic	✔	✔	✔
Secondary	Change in LV End-Systolic Volume	Echocardiographic	✔	✔	✔

CHF, chronic heart failure; KCCQ, Kansas City Cardiomyopathy Questionnaire; BNP, B-type Natriuretic Peptide; NT-proBNP, N-terminal pro-B-type Natriuretic Peptide; eGFR, estimated Glomerular Filtration Rate; HRV, Heart Rate Variability; ECG, Electrocardiogram; LVEF, Left Ventricular Ejection Fraction; E/A Ratio, Early to Late Ventricular Filling Velocity Ratio; LV, left ventricle.

The primary outcome of the SMART-CARE study is the relative reduction (≥20%) in hospital admissions, including emergency department visits and unplanned hospitalizations, over a six-month follow-up period in the intervention group compared to standard care (40). Hospitalization data will be collected prospectively and analysed for frequency, duration, and cause.

Secondary outcomes include:

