Quality of Life (QoL): Measured using KCCQ at baseline, 3 months, and 6 months.Biochemical parameters: BNP, NT-proBNP, serum creatinine, eGFR, and serum electrolyte levels (sodium, potassium, chloride) at 3 and 6 months.Functional parameters: Variations in HRV and RR derived from wearable sensor data.Echocardiographic measures: LVEF, Early to Late Ventricular Filling Velocity Ratio (E/A ratio), and left ventricular end-diastolic and end-systolic volumes, measured at 3 and 6 months.Adverse events: Incidence of therapy-related complications such as hypotension and bradyarrhythmias.These outcomes will provide a comprehensive evaluation of the impact of AI-driven remote monitoring clinical status, functional performance, biomarker trends, and patient-reported outcomes in individuals with CHF. The measurements collected by the minimally invasive devices will be uploaded to the “Smartcare” platform and analyzed using machine learning (ML) techniques to develop multiparametric scores capable of identifying the specific trajectory of patients affected by HF.

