#### Secondary endpoint analysis

2.6.2

Continuous variables will be presented as mean ± standard deviation (SD) for normally distributed data and as median and interquartile range (IQR) for non-normally distributed data. Categorical variables will be expressed as frequencies and percentages. The normality of distribution will be tested using the Shapiro–Wilk test. For normally distributed continuous variables, comparisons will be made using the paired t-test or one-way repeated measures ANOVA, depending on the situation. For non-normally distributed data, the Wilcoxon Signed-Rank test will be applied. Categorical variables will be compared using the Pearson chi-square test. Given the intrinsic differences in echocardiographic and clinical trajectories between HFrEF and HFpEF patients, all secondary endpoints (including echocardiographic parameters, biomarkers, and functional indices) will also undergo stratified analyses by LVEF phenotype. This approach is intended to avoid the dilution of clinically meaningful changes in subgroups with limited baseline variability, particularly among HFpEF patients. Subgroup analyses based on LVEF phenotype (HFrEF, HFmrEF, HFpEF) will be performed as exploratory analyses. The study is not powered to detect statistically significant differences between these subgroups; therefore, these analyses are intended to be descriptive and hypothesis-generating. To mitigate potential confounding when comparing phenotypes, LVEF category will be included as a covariate in multivariable models, and propensity score techniques will be applied when appropriate. Because echocardiographic parameters show markedly different baseline ranges and variability in HFrEF and HFpEF, echocardiographic secondary outcomes will also be interpreted within each LVEF phenotype. This approach is intended to avoid the dilution of true within-group changes in HFpEF patients, in whom structural parameters often fall within or near the normal range. A two-sided *p*-value < 0.05 will be considered statistically significant for all final analyses.

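### Within-phenotype change in LVEF is open to regression to the mean if the baseline echo sets the phenotype; report the device-versus-control difference instead

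*Protocol article*

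**What the plan says.** All quotes are from the protocol article.

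- **Stratification (2.6.2).** All secondary endpoints, echocardiographic ones included, "will also undergo stratified analyses by LVEF phenotype". The section adds that "echocardiographic secondary outcomes will also be interpreted within each LVEF phenotype" and gives the reason: "This approach is intended to avoid the dilution of true within-group changes in HFpEF patients".
- **LVEF as an outcome (2.4, Table 2).** "Change in LVEF" is a secondary outcome with ticks at baseline, 3 and 6 months. The E/A ratio and LV volumes are also listed ("left ventricular end-diastolic and end-systolic volumes, measured at 3 and 6 months").
- **Tests (2.6.2).** For normally distributed continuous variables, "comparisons will be made using the paired t-test or one-way repeated measures ANOVA, depending on the situation"; otherwise "the Wilcoxon Signed-Rank test will be applied". All of these compare a patient with himself or herself. No between-group test is named for continuous secondary outcomes. A two-sided 0.05 threshold applies to all final analyses.
- **Status and adjustment (2.6.2).** The phenotype subgroup analyses are labelled exploratory and unpowered. LVEF category, not continuous LVEF, is named as a covariate for multivariable models.
- **Source of the phenotype.** Section 2.6.1 lists LVEF phenotype among the baseline variables for the propensity score. No section says which echo assigns it or at what cut-offs.
- **Controls (2.1).** "All patients, regardless of group assignment, will be evaluated at baseline, 3 months, and 6 months".

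**The concern.** An LVEF reading is the patient's true value plus measurement error. Suppose one reading both places the patient in a stratum and serves as the starting value for change. Patients who read low by chance are then over-represented in HFrEF, and their next reading tends to be higher. Patients who read high by chance are over-represented in HFpEF, and their next reading tends to be lower. A paired test inside the stratum cannot tell this drift from real change.

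The plan adopts the within-stratum reading so that real change is not diluted. With strata set by the baseline echo, that reading would add apparent change of a predictable direction. At stake are the phenotype-specific LVEF results in the device group: improvement in HFrEF and decline in HFpEF could be reported, each with a small p-value, with no true change behind either.

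**Working it through.** The article gives no LVEF distribution, cut-offs, reading error or expected change, so there is no figure of its own to reproduce. Everything numerical below rests on stated assumptions.

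**Inputs from the article:** paired tests, two-sided 0.05, three phenotypes, 300 patients.

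**Assumptions:** cut-offs 40 and 50. Independent normal reading error with SD s = 3, 5 or 7 points. No true change. Four true LVEF distributions:
- A: normal, mean 45, SD 13.
- B: mixture of 50% N(32, 6), 20% N(45, 4) and 30% N(58, 5), written as N(mean, SD).
- C: better separated mixture of 50% N(30, 5), 20% N(45, 2) and 30% N(60, 5).
- D: normal, mean 44, SD 11.

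**Formula.** Let f be the density of the observed baseline LVEF X. With strata set by X, the expected follow-up minus baseline is

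- HFrEF: +s² · f(40) / P(X ≤ 40)
- HFpEF: −s² · f(50) / P(X ≥ 50)

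**Worked example (D, s = 5).** Observed SD = √(11² + 5²) = √146 = 12.08.
- HFrEF: f(40) = 0.03126 and P(X ≤ 40) = 0.3703, so the shift is 25 × 0.03126 / 0.3703 = +2.11 points.
- HFpEF: f(50) = 0.02919 and P(X ≥ 50) = 0.3097, so the shift is −25 × 0.02919 / 0.3097 = −2.36 points.

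**Results by simulation (D: shifts from the formula).** Each cell gives the spurious shift in HFrEF / HFpEF, then the rejection rate of the 5% paired t-test from the noncentral t distribution. The stratum size is 50 for A to C. For D it is 45 to 57, the expected stratum size in an assumed device group of 150.

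| Distribution | s = 3 | s = 5 | s = 7 |
|---|---|---|---|
| A | +0.7 / −0.7; 21% / 22% | +1.9 / −1.9; 47% / 47% | +3.4 / −3.4; 70% / 70% |
| B | +0.5 / −0.5; 12% / 15% | +1.3 / −1.6; 27% / 36% | +2.6 / −3.2; 48% / 65% |
| C | +0.3 / −0.4; 8% / 10% | +1.0 / −1.3; 17% / 26% | +2.2 / −2.7; 35% / 49% |
| D | +0.8 / −0.9; 29% / 30% | +2.1 / −2.4; 62% / 62% | +3.8 / −4.2; 85% / 86% |

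HFmrEF moves little under A to C (0 to −1.0 point). The direction in HFrEF and HFpEF is the same in every scenario. Size depends mainly on reading error and on how many patients lie near a cut-off.

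**Two checks on what removes the artefact.**
1. With strata set by an independent earlier reading, the mean change is within 0.03 points of zero and the test rejects at 5%.
2. With strata set by the baseline reading, but device and control groups drawn from the same distribution (A, s = 5), the difference in change between groups is 0.01 to 0.02 points.

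**Limit of the second check.** The cohorts are self-selected. If their true mean LVEF differs, the contrast adjusted for observed baseline LVEF keeps a residual of s²/(σ² + s²) per point of that difference, where σ is the true SD. For A with s = 5 this is 25/194 = 0.13. An assumed 3-point difference would leave about 3 × 0.13 = 0.39 points, against 1.9 points for the within-group artefact.

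**The case against.** **The article never says that the baseline echo assigns phenotype.** This stands. Section 2.1 requires confirmed CHF of any of the three types for at least six months, which can be read as a label fixed at diagnosis. On that reading the artefact has occurred before baseline and the expected shift is zero. Section 2.6.1 points the other way, but its list also holds prior hospitalizations, so it does not settle the matter. The point is therefore conditional.

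**Which echo is used is a detail an article may leave out.** Fair, and the omission alone would be no finding. What the article does fix is the within-stratum reading, the paired tests and the rationale. Together these are open to the artefact.

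**There is a control group.** A reader might infer that the plan will produce a false phenotype-by-device effect. The documents do not support that. The abstract's hypothesis is against standard care, controls have the same visits, and the drift arises in both groups and largely cancels when their LVEF distributions are similar. The misleading result comes from reading device-group change alone, which the named tests invite. Adjusting for LVEF category does not help inside a stratum, where category is constant.

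**This is a special case of relying on paired tests.** Largely so: a between-group comparison deals with most of it. It deserves separate mention because here the spurious change has a known direction that differs by phenotype.

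**The analyses are exploratory.** This lowers the importance, but the label deals with power and not with bias.

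**Conclusion.** The point holds in conditional form. If the study baseline echo assigns phenotype and within-group LVEF change is tested by stratum, the planned analysis can show LVEF rising in HFrEF and falling in HFpEF with no true change. The size is about 0.3 to 4 points for reading SDs of 3 to 7. False-positive rates are roughly 8% to 86% at about 50 patients per stratum, against a nominal 5%. The cut-offs, reading error and LVEF distributions are all assumed. At the low end the shift could go unnoticed.

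Two stronger readings go too far. The documents do not show that the artefact *will* occur, because they do not say which echo is used. Nor do they show that LV volumes are affected to a similar degree: volumes do not define the strata, and any effect depends on how their errors correlate with LVEF error, which was not examined.

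This concerns exploratory secondary results only and does not touch the primary endpoint. The change is worth making because it is cheap.

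**What to change.** In section 2.6.2:

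1. Base phenotype-specific LVEF results on the device-versus-control difference in change, adjusted for continuous baseline LVEF and not only LVEF category.
2. Do not test or interpret within-group LVEF change by stratum as an effect; show it descriptively if at all. Drop the rationale about true within-group changes for LVEF.
3. State which echo assigns phenotype, and the cut-offs.
4. Where an earlier echo exists, repeat the analysis with phenotype taken from it, as a sensitivity analysis. It is less suitable as the main rule: an earlier label may be out of date, and mixing earlier and baseline labels makes the strata inconsistent.

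**Cost.** A little more analysis work and, for item 4, the LVEF and date of an earlier echo. Intervals also widen: with equal groups the standard error of a difference in change is √2 times that of one group's change. With an SD of change of 6.9 and 50 patients per group, it goes from 6.9/√50 = 0.98 to 1.38 points. The cohorts are not randomized, so a small residual can remain if their true LVEF differs; the report should show baseline LVEF by group within each stratum.

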**Results:**

We hypothesize that AI-driven remote monitoring will significantly reduce hospitalizations, improve quality of life, and favorably impact biochemical and echocardiographic parameters compared to standard care.

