## Expected results

3

We anticipate that AI-based remote monitoring with the integration of wearable devices will lead to a ≥20% reduction in hospital admissions over six months compared to standard care. Furthermore, we expect improvements in secondary outcomes, including enhanced quality of life, reduced therapy-related adverse events, and more favourable trends in biochemical and echocardiographic parameters. By enabling early detection of clinical deterioration and supporting timely intervention, the SMART-CARE system is expected to offer a more proactive, individualized, and data-driven approach to managing CHF. These findings may support the integration of wearable technologies and AI into routine clinical practice for heart failure patients, potentially reducing the burden on healthcare systems and improving long-term patient outcomes.

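### Two-sided p<0.05 is made the success rule for all 15 secondary outcomes, with no hierarchy, adjustment or exploratory label on the whole-cohort analyses

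*Protocol article*

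**What the plan says.** The last sentence of section 2.6.2 reads: "A two-sided *p*-value < 0.05 will be considered statistically significant for all final analyses". It stands under the secondary-endpoint heading and has no stated exception.

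Table 2 ("SMART-CARE outcome measures by timepoint") marks 15 rows as secondary: KCCQ, adverse effects of therapy, BNP, NT-proBNP, creatinine, eGFR, sodium, potassium, chloride, HRV, respiratory rate, LVEF, E/A ratio and the two left ventricular volumes. Adverse effects are ticked at 6 months only. The other 14 are ticked at baseline, 3 and 6 months, in line with the text of section 2.4: "Both groups will undergo assessments at baseline, 3 months, and 6 months". The outcome list repeats both follow-up times for the laboratory measures ("serum electrolyte levels (sodium, potassium, chloride) at 3 and 6 months") and for the echocardiographic ones. No outcome or time point is put first.

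For normally distributed continuous outcomes, section 2.6.2 says that "comparisons will be made using the paired t-test or one-way repeated measures ANOVA, depending on the situation". It describes no multiplicity step. The LVEF-phenotype subgroup analyses are set apart as exploratory: "therefore, these analyses are intended to be descriptive and hypothesis-generating". The whole-cohort secondary analyses carry no such label.

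The Abstract hypothesises that monitoring "will significantly reduce hospitalizations, improve quality of life, and favorably impact biochemical and echocardiographic parameters compared to standard care". Section 3 adds: "we expect improvements in secondary outcomes, including enhanced quality of life, reduced therapy-related adverse events, and more favourable trends in biochemical and echocardiographic parameters".

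**The concern.** The article does not leave multiplicity open. It fixes full alpha for every final analysis, lists many outcomes, and does not make a secondary claim depend on the primary result. It also says in advance which secondary benefits it expects. A team following the text could miss the primary endpoint, find one biomarker, echocardiographic index or quality-of-life score below 0.05, and report it as a statistically significant benefit of the system. With this many chances, the error rate of such a claim is well above that of a single test.

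**Working it through.** **Inputs**
- Per-test threshold: 0.05 two-sided (section 2.6.2), which is 0.025 in the favourable direction.
- Secondary outcomes: 15 (Table 2).
- Outcome-by-time tests, if 3 and 6 months are tested separately: 14 × 2 + 1 = 29.
- A smaller family of 13, if HRV and respiratory rate are left out. Section 2.4 derives them from wearable data, and section 2.2 gives the control group no remote monitoring.

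The 0.05 threshold is a chosen rule and the article states no family-wise rate, so there is no figure of the plan to reproduce.

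**Independent tests, no true effect on any outcome**

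The chance of at least one false positive among m tests is 1 − (1 − a)^m, with a = 0.025 for the favourable direction and a = 0.05 for either direction.

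| m | Favourable direction | Either direction |
|---|---|---|
| 13 | 1 − 0.975^13 = 28.1% | 1 − 0.95^13 = 48.7% |
| 15 | 1 − 0.975^15 = 31.6% | 1 − 0.95^15 = 53.7% |
| 29 | 1 − 0.975^29 = 52.0% | 1 − 0.95^29 = 77.4% |

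The expected number of false positives in either direction is 15 × 0.05 = 0.75, or 29 × 0.05 = 1.45.

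**Correlated tests**

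The article gives no correlations, so a range is shown. These figures come from simulated normal test statistics (200,000 draws, cut-off 1.96). For 15 tests with one common correlation:

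| Correlation | Favourable direction | Either direction |
|---|---|---|
| 0.2 | 26.2% | 49.7% |
| 0.5 | 18.1% | 36.0% |
| 0.8 | 10.1% | 20.2% |

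A second simulation took 29 tests and clustered only related markers: BNP with NT-proBNP, creatinine with eGFR, sodium with chloride, and LVEF with the volumes. Within-cluster correlation ran from 0.5 to 0.95, and correlation between 3 and 6 months from 0.5 to 0.9. The favourable-direction figure then lies between 33% and 47%.

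**Comparison**

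One two-sided test at 0.05 has a 2.5% chance of a false favourable result. The smallest value above, 10.1%, is about four times that (10.1 / 2.5 = 4.0).

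**The case against.** **A separate statistical analysis plan may handle multiplicity.** It may, and silence in an article would be no finding. But the published sentence covers all final analyses. A later hierarchy would contradict it, so it needs changing either way.

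**The study is a non-randomised cohort with one primary endpoint, and adjusting secondary outcomes is a choice.** This stands in part. The primary alpha is not inflated, and no rule obliges the sponsor to control error across secondary outcomes. What is lacking is a statement that these results are supportive.

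**The expected-benefit wording is not a decision rule.** This is fair. In the Abstract, the word for significance attaches to hospitalizations, and section 3 speaks of expectations. The passages show how the secondary results are meant to be read; they do not define success.

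**The count of 29 is assumed.** This is correct. A single repeated-measures test per outcome gives 15, and dropping the two wearable-derived measures gives 13. So 29 is an upper count.

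**Three stronger readings are tempting but not supported.**
- A reader might take 54% or 77% as the chance of a false improvement. Those figures count either direction; the matching ones are 32% and 52%, less with correlation.
- A reader might say that section 2.6.2 contradicts itself by calling the phenotype analyses descriptive and then applying p<0.05 to everything. The specific statement can be read as qualifying the general one, so this is at most a loose end to tidy.
- A reader might take the percentages as the error rate for a claim against standard care. For continuous outcomes the named tests (paired t-test, repeated-measures ANOVA, Wilcoxon signed-rank) compare a patient with himself or herself, and allocation follows willingness to wear the device. The error rate of a between-group claim from such tests is not given by this calculation.

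**Conclusion.** The point holds as a weakness in a stated rule. As written, section 2.6.2 allows any of 15 secondary outcomes to be declared statistically significant at full alpha, even if the primary fails, and nothing marks the whole-cohort results as exploratory.

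The size is a chance of about 32% of at least one false favourable finding with 15 independent tests, falling to 18% and 10% at correlations of 0.5 and 0.8. It is about 28% for 13 independent tests and rises to 52% for 29. Counting either direction, the independent figures are 54%, 49% and 77% for 15, 13 and 29 tests.

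These figures assume no true effect on any outcome, valid 5% size for each test, and one favourable direction per outcome, which the article does not define. They do not touch the primary endpoint. The issue is moderate: the text should be corrected, but the design does not depend on it.

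**What to change.** Replace the last sentence of section 2.6.2 so that two-sided p<0.05 is a significance criterion for the primary endpoint only. State there that all secondary outcomes, all 3-month comparisons and all LVEF-phenotype strata are supportive or exploratory. They should be reported as estimates with 95% confidence intervals and nominal p-values, and cannot establish benefit if the primary fails. Bring the wording on expected benefits in the Abstract and section 3 into line.

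If the sponsor wants a confirmatory secondary claim, there are two routes:
- Name in advance one outcome and one time point of its choice, analyse it as a between-group comparison, and test it at 0.05 only if the primary is significant. The documents do not rank the secondary outcomes, so the choice is the sponsor's.
- Apply Holm's procedure across the 6-month set. With 15 outcomes, the smallest p-value is then compared with 0.05/15 = 0.0033.

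The cost is a few sentences, with no further patients or data. The downside is small: fewer secondary results can be called statistically significant. The change should be made before results are seen.
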